### Sequence generation and random assignment

2.7.

Block randomization will be performed, and the block length will be randomly set to any one of 4/6/8. The randomization of block length and intrablock randomization will be generated using EXCEL random numbers. The intrablock randomization values will be set to 1 and 2, representing two groups. The function formula is fx = RANDBETWEEN (1,2), and the block length randomization function formula is fx = 2 * RANDBETWEEN (2,4).

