**Methods:**

This study is a prospective, superiority, multicenter, non-masked, randomized controlled trial that investigates the outcome and hospitalization medical expense of SINTNP compared to TNP for PE. A total of 320 eligible patients according to sample size calculation by retrospective data will be randomly assigned to the SINTNP group or the TNP group at a 1:1 ratio using stratified blocked randomization and the zone length was set as four. Patients aged between 3 and 18 years old for the first surgery and without combination of complex anomalies such as Marfan syndrome and congenital heart disease will be considered for the study. The co-primary endpoint is thoracic related complications and medical expense during hospitalization. Thoracic related complications were defined as pneumothorax, pleural effusion, pneumonia and incision infection. The secondary endpoints include surgery duration and length of hospital stay.

The registration number for this study protocol is ChiCTR230073081 (Chinese Clinical Trial Registry, A Primary Registry of International Clinical Trial Registry Platform, World Health Organization).

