### Trial design and study setting

2.2.

The study is a multicenter, non-masked, randomized controlled trial including patients with PE aged between 3 and 18 years old for the first surgery and without a combination of complex anomalies.

The participants will be randomly assigned to the SINTNP or TNP group with a balance of 1:1. Participants will be allocated as evenly as possible to four hospitals in western China. The sponsor institution was Children's Hospital of Chongqing Medical University. This multicenter study will also be conducted in Chengdu Women and Children's Central Hospital, Chongqing Three Gorges Central Hospital and Qujing Maternal and Child Health Hospital.

Due to objective conditions, the participants in the four centers cannot be completely balanced, but the participants in any center will not exceed 50% of the total number or be less than 15% of the total number. Independent statisticians will perform noninferiority tests for comparisons of SINTNP to TNP.

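### The printed formula in section 2.7 is simple randomisation and does not produce balanced blocks, and the abstract and section 2.7 give different block lengths

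*Protocol article*

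**What the plan says.** The abstract describes allocation "at a 1:1 ratio using stratified blocked randomization and the zone length was set as four"; zone length evidently means block length. Section 2.2 (Trial design and study setting) repeats the ratio: "The participants will be randomly assigned to the SINTNP or TNP group with a balance of 1:1". It also spreads recruitment over four hospitals, each contributing between 15% and 50% of the total.

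Section 2.7 (Sequence generation and random assignment) gives the working rule. On block length: "Block randomization will be performed, and the block length will be randomly set to any one of 4/6/8". On the content of a block: "The intrablock randomization values will be set to 1 and 2, representing two groups". The Excel formulas follow: "The function formula is fx = RANDBETWEEN (1,2), and the block length randomization function formula is fx = 2 * RANDBETWEEN (2,4". The section does not mention shuffling a balanced list, redrawing an unbalanced block, or filling the rest of a block once one arm is complete.

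Section 2.8 has the generated sequence placed in numbered, sealed, opaque envelopes. Section 2.11 compares continuous outcomes by an unpaired t test or Mann-Whitney test, and adds an analysis across centres to judge bias and reliability. Section 2.6 sizes the trial on hospital expense.

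**The concern.** A block keeps the arms level because its contents are fixed in number (half of each code) and only their order is random. The formula in section 2.7 fixes nothing. Each cell is a separate coin flip, so where one block ends and the next begins makes no difference to the sequence. A statistician who followed the section literally would produce a simple random list labelled as blocks.

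The two descriptions of block length also cannot both be carried out: a fixed length of four is not a length drawn from 4, 6 and 8.

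Balance within hospitals is what is at stake. The outcome that sizes the trial is the hospital bill, collected at four hospitals, and the planned two-group test does not adjust for hospital. If charges differ between hospitals, an uneven split within a hospital moves the arm difference by chance. Blocking within hospitals would largely prevent that.

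**Working it through.** **Inputs from the article.** Total 320, 160 per group, at least 141 evaluable per group, withdrawal and dropout 10% to 15%, mean costs 30,250 and 28,157 RMB, SD 2,000, margin 1,500 (abstract and section 2.6). Smallest centre 15% of 320 = 48 children (section 2.2). Block lengths 4, 6 and 8 (section 2.7).

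**Assumptions.** One-sided alpha 0.05 and 80% power. The article states neither; they are used because they reproduce its figure.

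**The plan's own figure.** Effect beyond the margin: 30,250 − 28,157 − 1,500 = 593 RMB. Per group n = 2 × (1.645 + 0.842)² × 2,000² / 593² = 140.7, rounded up to 141. This agrees. Inflating 141 for loss gives 157 at 10% and 166 at 15%, so 160 lies within the stated range.

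**Balance of a block under the printed formula.** P(balanced) = C(b, b/2) / 2^b.
- b = 4: 6/16 = 37.5%
- b = 6: 20/64 = 31.3%
- b = 8: 70/256 = 27.3%

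With the three lengths equally likely the average is 32%, so about two thirds of blocks are unbalanced. A block of four falls entirely in one arm with probability 2/16 = 12.5%.

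**Balance of the trial and of a centre.** Arm size follows Binomial(n, 0.5).
- n = 320: 95% range 142 to 178; P(exactly 160:160) = 4.5%.
- n = 48: 95% range 17:31 to 31:17; P(arms differ by 10 or more, that is 60:40 or worse) = 19%.

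**Cost in power.** Power = Φ(593 / (2,000 × √(1/n₁ + 1/n₂)) − 1.645), with both arms reduced by 10% loss.
- 160:160 randomised: 80.8%
- 142:178 randomised: 80.4%
- averaged over all splits of Binomial(320, 0.5): 80.7%

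The average loss is about 0.1 percentage point.

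**Cost in random error from a centre imbalance (illustration).** Suppose one 48-child centre splits 31:17 and the other 272 children split 136:136, so the arms are 167:153. That centre makes up 31/167 = 18.6% of one arm and 17/153 = 11.1% of the other. The arm difference then moves by 0.075 times the gap between that centre's charges and the rest. The article gives no costs by centre. For assumed gaps of 1,000 to 4,000 RMB the shift is about 75 to 300 RMB, or 13% to 50% of the 593 RMB, and it can go in either direction.

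**With true permuted blocks.** Every completed block is balanced. The imbalance in one list is at most half the longest block: 2 with blocks of four, 4 with blocks of 4/6/8. Over four centre lists the arms differ by at most 8 or 16, and only through unfinished last blocks. The sample size is unchanged.

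**The case against.** The strongest reply is that simple randomisation is a valid method. It is unbiased and 1:1 in expectation, and with 320 children it rarely goes far wrong. That stands, and it limits the point in several ways.

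- **Power.** A reader might note that the smaller arm falls below 157 with probability about 70% and infer that the trial will usually be underpowered. The arithmetic does not support this. The threshold is only three below the planned 160, and power depends on both arms together; even 142:178 keeps 80.4% after 10% loss. At 15% loss a perfect 160:160 would itself miss the 166 needed, which is a matter of dropout inflation and not of randomisation.
- **Confounding.** A reader might infer that hospital price level biases the comparison. Chance imbalance by centre is random error and not systematic confounding, a price gap between hospitals is assumed, and section 2.11 plans some analysis across centres.
- **Strata.** Section 2.7 is silent on stratification, but silence does not contradict the abstract. A condensed article may leave the factor and the centre lists to the full protocol.
- **Recalculation.** Excel redraws random cells when a sheet recalculates. Section 2.8 nevertheless fixes the sequence on paper in sealed envelopes, and freezing the sheet is detail that an article may omit.
- **Unreported step.** The investigators may redraw unbalanced blocks or force the remainder. If so, the list is sound and the text is incomplete. The documents therefore do not show that the actual list lacks blocks; they show that the stated rule does not produce them.

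None of this answers the two core facts. The only formula printed for assignments within a block does not deliver block randomisation, and the two block lengths conflict.

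**Conclusion.** The point holds in limited form. As written, section 2.7 specifies simple randomisation under the name of block randomisation: about two thirds of blocks would be unbalanced, one arm of 320 would range from 142 to 178, and a 48-child centre from 17:31 to 31:17. The abstract and section 2.7 contradict each other on block length.

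The allocation is not biased, and the sample size is not materially threatened. The power figures rest on an assumed one-sided 0.05. The real loss is the claimed balance, mainly within centres, and its effect on the cost comparison depends on differences in charges between hospitals that the article does not report. It still deserves correction before recruitment, because an allocation list cannot be repaired once used.

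**What to change.** Before the first envelope is opened, replace the assignment formula. For each block of length b, write b/2 ones and b/2 twos, sort them by a random key or use a seeded program, and freeze and archive the values. Produce one list, and one envelope series, per stratum of the stratification that the abstract already claims. The article does not name the factor; centre is the natural choice. State a single block-length scheme in both the abstract and section 2.7. If a balancing step is already in use but was not reported, describing it would be enough in place of a new formula.

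The work is small: a regenerated list and a few corrected sentences, with no change to the sample size. Section 3 says that the study has not started. Section 2.13 forbids any change to the protocol after publication, so the change needs a documented, published correction and cannot be a silent edit.

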### Allocation concealment and implementation

2.8.

In each center, an authorized research nurse in the clinical unit will be responsible for recruiting the patient. All of the children's guardians signed a consent form. The envelope method will be used for allocation concealment, and the generated random allocation sequence will be placed in a sequentially encoded, sealed, and opaque envelope by Allocator 1. Allocator 1 will be unaware of the corresponding groups represented by randomized values 1 and 2 in advance. After determining the eligibility of the test subjects, Allocator 2 will open the envelopes in order and assign the test subjects to the corresponding experimental groups. After completing the allocation, the allocator will withdraw from this study and will not communicate with any participants or medical staff.

### Masking

2.9.

Radiologists, nurses, and data analysts will be blinded to group information. The label of group was open for doctors and family members of children's guardians. The outcome will be assessed blindly by a statistician who is blinded to the group information. After data analysis, the results of the group information will be unblinded by the director of the trial. At this point, all participants in the study can receive detailed labels of grouping information.

### Data collection and management

2.10.

A case report form (CRF) will be created in advance. All data will be entered into the CRF first, and then double data entry will be used to input data into the computer.

Each medical center will designate two investigators to gather patient baseline, outcome, and other relative trial data by electronic medical record. All electronic data and paper-based materials will be summarized. The characteristic table is shown in Table 2.

**Table 2 T2:** Characteristic table of individual patients.

Characteristic	Age (years old)	Gender	Haller index	Pulmonary function	Cardiac function	Expenses during hospitalization (RMB/Yuan)	Thoracic-related complications	Surgery duration (minutes)	Length of hospital stay (day)
		Male		Normal	Normal		Pleural effusion		
		Female		Abnormal	Abnormal		Pneumothorax		
							Pneumonia		

Abnormal lung function is defined as (FEV1) less than 80% predicted value or FVC less than 80% predicted value or FEV1/FVC less than 92% predicted value.

Abnormal cardiac function is defined as mitral valve prolapse or arrhythmia.

All researchers underwent standardized training in advance to ensure that their medical services and data collection were standardized and that there were no significant differences between researchers. Only researchers who have passed the assessment of committee board can join this study. During the patient recruitment stage, all communication regarding the research background and process is strictly carried out in accordance with the section in the informed consent form. HL, LZ, YX and LX were members of the research committee board and are responsible for coordinating the entire research and handling difficulties such as inconsistent data. A multicenter meeting will be held every two weeks to ensure the smooth progress of the research.

### Statistical methods

2.11.

Continuous data will be presented as the means with standard deviations (SDs) or medians with interquartile ranges (IQRs). The Kolmogorov–Smirnov test will be used to evaluate normality. Continuous data will be compared between the two groups by unpaired t test (normal distribution) or the Mann‒Whitney *U*-test (nonnormal distribution). A chi-square test will be used to compare categorical variables between two groups. Pre-protocol analysis (PP) will be performed with data of participants finishing the whole study and intention to treat analysis (ITT) will be used in full analysis set. Inter group analysis across centers were performed to evaluate the influence of bias and the reliability of the overall study.

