### Sample size and recruitment

2.6.

Medical expense during hospitalization is the primary outcome indicator of this study because it can objectively evaluate the financial burden of the patient's family. Based on our retrospective research data on surgeries over the past three years, the average cost of the TNP group was 30,250 RMB, while the average cost of the SINTNP group was 28,157 RMB. The standard deviation will be set as 2,000, and the superiority margin will be set as 1,500. The sample size will be calculated to require at least 141 children in each group.

The proportion of thoracic-related complications was approximately 9.6% in SINTNP and 13.6% in nonthoracoscopic-assisted Nuss surgery with double incision. The sample size calculation requires over 3,000 people per group according to the proportion of thoracic-related complications, and currently, we are unable to recruit so many patients. We will truthfully describe this recruitment-related limitation in the officially published article. Considering a 10% to 15% withdrawal and dropout rate, each group will ultimately include 160 children.

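### The co-primary expense comparison is unadjusted although age, sex and Haller index are recorded: valid as planned, but it may forgo power against the 1,500 RMB margin

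*Protocol article*

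**What the plan says.** All references are to the protocol article.

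- **Analysis (2.11).** "Continuous data will be compared between the two groups by unpaired t test (normal distribution) or the Mann‒Whitney" test when the distribution is not normal. Hospital expense is continuous and is one of the two co-primary outcomes (2.1.1, 2.5.1), so it falls under this rule. The section names no covariate and no centre term. Its only further step on centres is a separate comparison across them.
- **Data (2.10).** "Each medical center will designate two investigators to gather patient baseline, outcome, and other relative trial data by electronic medical record". Table 2 has a column for each of age, gender, Haller index, pulmonary function and cardiac function, at the level of the individual patient.
- **Population and allocation (2.2).** The trial enrols "patients with PE aged between 3 and 18 years old for the first surgery" at four hospitals, each contributing between 15% and 50% of the total. Allocation is 1:1.
- **Sizing (2.6).** The planning means, from retrospective data, are 30,250 RMB for TNP and 28,157 RMB for SINTNP. Spread and margin are fixed as follows: "The standard deviation will be set as 2,000, and the superiority margin will be set as 1,500". From these the plan derives a minimum of 141 per arm, which it raises to 160 to allow for losses of 10% to 15%.

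**The concern.** An unpaired t test or a Mann-Whitney test leaves all the variation in cost between children in the error term. The children range from 3 to 18 years. They qualify through any two of seven indications (2.3.1) and go home when pain score, a walking test and a radiograph allow it (2.4). It is reasonable, though only an inference, that age and severity of deformity explain part of the bill.

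The sample size leaves little reserve. The expected saving exceeds the margin by 593 RMB against an SD of 2,000. If baseline values that are already collected explain some of that variance, a model that uses them would give a narrower confidence interval for the saving. It would also take out of the estimate the part of any chance imbalance that those values carry.

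**Working it through.** **Inputs from 2.6.** Mean expense 30,250 RMB (TNP) and 28,157 RMB (SINTNP), SD 2,000, margin 1,500, 141 per group, 160 after allowance for dropout. Alpha, sidedness and power are not stated.

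**Input assumed.** R-squared, the share of within-arm cost variance that the baseline covariates explain. The documents give none, so a range is shown.

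**1. Reproduce the plan's sample size.**

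- Difference: 30,250 − 28,157 = 2,093 RMB. Beyond the margin: 2,093 − 1,500 = 593 RMB.
- n per group = 2 × (z_alpha + z_power)² × SD² / 593².
- One-sided 5%, 80% power: 2 × (1.645 + 0.842)² × 2,000² / 593² ≈ 140.7, so 141. This matches.
- Two-sided 5% at 80% power gives 179, and one-sided 5% at 90% gives 195. Neither matches.

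The plan's figure is therefore that of an unadjusted margin test at one-sided 5% and 80% power. These settings are inferred from the match.

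**2. Power of the planned test.** The standard error is 2,000 × √(2/n), and power = Φ(593/SE − 1.645).

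- n = 141: SE = 238.2, 593/238.2 = 2.490, power 80.1%.
- n = 160: 84.3%.
- n = 136 (160 less 15%): 78.8%.

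**3. Power with adjustment.** The residual SD is 2,000 × √(1 − R²), so power = Φ(2.490/√(1 − R²) − 1.645) at 141 per group.

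| Assumed R² | Power, one-sided 5% | Gain (points) |
|---|---|---|
| 0 | 80.1% | – |
| 0.05 | 81.8% | 1.7 |
| 0.10 | 83.6% | 3.5 |
| 0.16 | 85.8% | 5.7 |
| 0.25 | 89.1% | 9.0 |

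**4. Price of the covariates.** Three centre terms, age and Haller index make five terms. An approximate penalty multiplies the standard error by √(279/274) = 1.009.

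- R² = 0: 79.5%, a loss of about half a point.
- R² = 0.02: 80.2%, which is break-even.
- R² = 0.10: 83.0%.

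The figures in step 3 are thus about half a point generous.

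**5. Which hypothesis gains.** Against a difference of zero (2,093 RMB), unadjusted power already exceeds 99.9% at 141 per group. Any gain concerns only the test against the margin, which is the test that 2.6 sizes the trial for.

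**6. Chance imbalance.** At 160 per group, an imbalance of 1.96 standard errors in one covariate is 1.96 × √(2/160) = 0.219 SD. If that covariate correlated 0.4 with cost (assumed), the estimated saving would shift by 0.219 × 0.4 × 2,000 ≈ 175 RMB. The standard error of the unadjusted difference is 2,000 × √(2/160) ≈ 224 RMB, so this shift is about 0.78 of one standard error.

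**The case against.** The strongest reply is that nothing here is wrong. Under 1:1 randomization the t test keeps its type I error, its standard error already allows for chance imbalance, and the sample size was calculated for exactly this test. All of that stands.

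It can also be said that the covariates may predict little. An SD of 2,000 on means of 28,157 to 30,250 is a coefficient of variation of about 7%. Children who need two bars are withdrawn, severe combined malformations are excluded, and anaesthesia, analgesia and discharge follow one pathway. This stands too, and it is why the gain must remain conditional.

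A third reply is that adjusted models are commonly left to a statistical analysis plan. That holds for supporting analyses. Here, however, the article itself names the test for the outcome, and 2.13 bars changes to the protocol after publication.

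Three stronger readings are tempting and are not supported:

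- **That the trial does lose power.** No section links age, sex, Haller index, or lung or cardiac function to expense.
- **That power is only 70.2%.** This is the two-sided 5% figure at 141 per group. That criterion would need 179 per group and does not match the plan's sizing.
- **That chance imbalance biases the saving.** The 175 RMB in step 6 is about 30% of 593 RMB, but it rests on an assumed correlation and on an imbalance that a given covariate reaches, in either direction, in only 5% of trials. It is ordinary sampling error that the unadjusted interval already covers.

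**Conclusion.** The point holds as a missed efficiency gain. The planned expense test is valid and consistent with its sample size, but it cannot use baseline values that the trial already collects. It may therefore forgo power against the 1,500 RMB margin.

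The gain depends wholly on an R-squared that the documents do not give. At 141 per group and one-sided 5% it runs from 1.7 points (R-squared 0.05) to 9.0 points (0.25) before the small degrees-of-freedom penalty, and it vanishes at about 0.02 or below. The one-sided 5% level and the 80% power are inferred from the reproduced sample size. The SD of 2,000 is taken as the within-group SD.

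The change is worth making because it is cheap and its downside is about half a point of power. The trial does not depend on it.

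**What to change.** In 2.11, make the primary analysis of hospital expense a prespecified linear regression of expense on arm, with centre, age (continuous) and Haller index (continuous), and with heteroscedasticity-robust standard errors. Sex may be added. Report the adjusted mean difference in RMB with its confidence interval, judge it against the 1,500 RMB margin, and keep the unpaired t test as a sensitivity analysis.

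Centre belongs in the model because the design points to it more clearly than to any patient-level value: there are four hospitals of unequal size, the abstract calls the randomization stratified (without naming factors), and 2.11 already plans a look across centres. Lung function should stay out of the primary model unless it is complete. Some young children may be unable to perform the test, so missing values would track age.

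The cost is a sentence or two of text, a few degrees of freedom and simple imputation for any missing baseline value. No new patients, visits or data are needed. The model must be fixed before outcome data are seen, since covariates chosen afterwards would carry little weight. Because 2.13 forbids changes after publication, the sponsor would need to record openly how this prespecification fits with that rule. The article's Results section says that the formal study had not started when it was written.

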#### Coprimary outcomes

2.5.1.

Thoracic-related complications include pleural effusion, pneumothorax, and pneumonia diagnosed on chest radiograph.

Medical expenses during hospitalization are the total expenses recorded in the hospitalization electronic system, all of which are the original expenses before insurance reimbursement and are denominated in RMB.

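### Hospital expense is sized on a mean saving beyond 1,500 RMB, but is compared by a normality-gated t test or Mann-Whitney test with no centre term

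*Protocol article*

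**What the plan says.** Protocol article, section 2.11 (Statistical methods), sets one rule for every continuous outcome. A Kolmogorov-Smirnov "test will be used to evaluate normality". Then: "Continuous data will be compared between the two groups by unpaired t test (normal distribution", with Mann-Whitney if the data are judged non-normal. Centre appears once in that section: "Inter group analysis across centers were performed to evaluate the influence of bias and the reliability of the overall study".

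Expense falls under this rule. Section 2.6 says: "Medical expense during hospitalization is the primary outcome indicator of this study". It bases the sample size on mean costs of 30,250 RMB (TNP) and 28,157 RMB (SINTNP), an SD set at 2,000 and a superiority margin of 1,500, giving at least 141 per group and 160 after dropout. Section 2.5.1 defines the outcome: "Medical expenses during hospitalization are the total expenses recorded in the hospitalization electronic system".

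Four hospitals take part. Section 2.2 says: "Due to objective conditions, the participants in the four centers cannot be completely balanced", and allows each between 15% and 50% of participants. The abstract describes allocation "using stratified blocked randomization and the zone length was set as four", without naming the stratification factor. Section 2.7 describes blocks but no strata.

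**The concern.** There are two separate problems.

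1. **The quantity tested.** The sized hypothesis concerns a difference in means against 1,500 RMB. A Mann-Whitney test as written addresses no difference in ranks against zero. Which of these the trial reports would depend on a normality test run on the trial's own data. Section 2.6 justifies expense as a measure of the family's financial burden, which is a question about mean RMB.

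2. **Centre.** Total charges from four hospitals are pooled with no centre term. If hospitals differ in cost level, that spread counts as noise in the arm comparison. Only 2,093 − 1,500 = 593 RMB, about 0.30 SD, has to be detected beyond the margin, so added variance is costly. A separate look across centres leaves the primary estimate and its standard error unchanged.

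**Working it through.** **Inputs.** From section 2.6: means 30,250 and 28,157, SD 2,000, margin 1,500, n = 141 per group. Alpha, sidedness and power are not stated; they are inferred in step 1. The between-centre SD, b, is an assumption throughout.

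**1. Reproduce the stated sample size.** n = 2(z_α + z_β)² SD² / (difference − margin)². At one-sided 5% and 80% power: 2 × (1.645 + 0.842)² × 2,000² / 593² = 140.7, so 141, an exact match. One-sided 2.5% or two-sided 5% gives 179 at 80% power. One-sided 5% at 90% power gives 195. A zero null gives 12 to 20. The stated figure is therefore a margin test on means.

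**2. Unadjusted power if 2,000 is the within-centre SD.** Total SD = √(2,000² + b²); SE = total SD × √(2/141); power = Φ(593/SE − 1.645).

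| b (RMB, assumed) | Total SD | SE | Power, margin test | n per group for 80% |
|---|---|---|---|---|
| 0 | 2,000 | 238 | 80% | 141 |
| 500 | 2,062 | 246 | 78% | 150 |
| 1,000 | 2,236 | 266 | 72% | 176 |
| 1,500 | 2,500 | 298 | 64% | 220 |
| 2,000 | 2,828 | 337 | 55% | 282 |

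A simulation with 282 children and assumed centre shares of 40/25/20/15%, run at b = 0, 1,000, 2,000 and 3,000, gave power of 78% to 81% for a linear model with centre.

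**3. If 2,000 already includes centre spread.** The first row applies to the unadjusted test: 141 stands, and adjustment reduces the residual SD and adds power.

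**4. Zero null.** A two-sided 5% t test against zero uses Φ(2,093/SE − 1.96). At b = 2,000 this is Φ(6.21 − 1.96), and power stays above 99% across the table.

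**5. Type I error at the margin.** If allocation is stratified by centre, the unadjusted standard error is too large. In the same simulation, type I error against a nominal 5% was 3.1% at b = 1,000 and 1.2% at b = 2,000. Without such stratification it stayed near 5%.

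**6. What the rank branch estimates under skew.** Assume an exponential extra cost in complicated cases, on a base SD of 1,500. Take complication rates of 13.6% for TNP and 9.6% for SINTNP; section 2.6 gives the 13.6% for a double-incision non-thoracoscopic procedure, so it is only a stand-in for TNP. The true mean saving is 2,093 + 0.04 × mean extra cost.

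| Mean extra cost (RMB, assumed) | True mean saving | Hodges-Lehmann shift (simulated) |
|---|---|---|
| 5,000 | 2,293 | about 2,180 |
| 10,000 | 2,493 | about 2,200 |
| 20,000 | 2,893 | about 2,210 |

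The rank-based shift barely moves while the mean saving grows. Kolmogorov-Smirnov rejected normality in roughly 88% to 100% of simulated TNP samples of 141. These tails imply a TNP-arm SD of about 2,900 to 10,000, well above the planned 2,000.

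**7. Centre mixture without skew.** With four equal centres, normal within-centre costs (SD 2,000) and about 140 per arm, a normality test allowing for estimated parameters (Lilliefors) rejects in about 3% to 4% of samples at b = 1,000, 6% at 1,500 and 12% to 13% at 2,000. The plain Kolmogorov-Smirnov test rejects in about 2% or fewer.

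**The case against.** The strongest reply is that the power loss is assumed rather than documented. A reader might infer that the SD of 2,000 comes from the sponsor's own hospital and that price differences must add to it. Section 2.6 ties only the two means to retrospective data, gives no source for the SD, and does not say how many hospitals supplied the data. No document reports price differences between the four hospitals, and at b = 500 the loss is only 2 points. This stands: the power figures are conditional.

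A reader might also expect pooled charges from four hospitals to fail the normality test through mixture alone. Step 7 shows that this is uncommon. The rank branch becomes likely only with real skew, such as long or complicated stays, which the documents do not quantify.

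Saying that the plan ignores centre altogether would be too strong, because section 2.11 does plan an across-centre analysis. What that does not do is adjust the primary comparison. Nor is there a risk of false claims of superiority: under centre-stratified allocation the unadjusted test is conservative, and the abstract does not name centre as the stratum. Finally, the power loss applies only to the margin test, and section 2.11 never says how the margin enters the analysis.

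A fuller adjustment model may sit in an analysis plan not shown. But section 2.11 does more than stay silent: it fixes the gate and both tests. The mismatch between a rank test and a mean margin needs no assumption about centres, so it survives all of these replies.

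**Conclusion.** The point holds in a limited form. The gated rule does not match the hypothesis that set the sample size. If skew sends expense to Mann-Whitney, the trial would neither estimate the mean saving in RMB nor test the 1,500 RMB margin. How likely that is depends on skew that the documents do not describe.

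The missing centre term is a matter of efficiency. Its cost ranges from nothing at b = 0 to about 25 points of power at b = 2,000 (80% to 55%), provided that 2,000 is a within-centre SD and that the margin test at one-sided 5% is the intended one. The documents do not support reading this as an established loss of power or as inflated type I error. The change is worth making; confidence is moderate.

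**What to change.** In section 2.11, prespecify for expense a linear model in RMB with arm and centre as fixed effects. Report the adjusted mean saving (TNP minus SINTNP) with robust or bootstrap confidence limits, whatever the normality test shows, and compare the lower limit with 1,500 RMB. Keep Mann-Whitney as a sensitivity analysis. Extending centre adjustment to the other outcomes is optional.

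This takes a few lines, no new data (each child's hospital is known) and three degrees of freedom. Section 2.13 bars protocol changes after publication, so the sponsor would need to record the change openly, in a dated analysis plan or amendment, before the group labels are unblinded.
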